### Statistical analysis

#### Sample size calculation

Based on the most recent meta-analysis of MBCT in IBD, we anticipate the effect size of the reduction of psychological distress to be Cohen’s *d* = 0.51 [17]. With an error probability of 0.05, 0.80 power and a 1:1 allocation ratio, the required total sample size is 98. To account for dropout, we looked at dropout rates in the two similar RCTs of MBIs in patients with IBD, which were 11.5% [18] and 44% [19], respectively. These rates were averaged, i.e. 28%. Using the formula N = n/(1-(z/100)), our corrected sample size is N = 136 (n = 68 per condition).

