Although the available evidence on the effectiveness of MBIs for IBD is still relatively scarce, a meta-analysis, which included 477 patients in eight randomised controlled trials (RCTs), showed significant benefits in terms of psychological distress and QoL [17]. However, the variety in MBIs was rather high, none of the studies had psychological distress as primary outcome, and most studies suffered from methodological limitations such as small sample size, incomplete data reporting and a lack of fidelity measures. Looking specifically to the available RCTs using Mindfulness-Based Cognitive Therapy (MBCT) or Mindfulness-Based Stress Reduction (MBSR) in IBD patients, it was limited to two studies [18, 19]. Jedel et al. included patients with a recent flare of ulcerative colitis and found no difference in disease course between the MBSR and control groups, although patients in the intervention group experienced less stress during a flare in the follow-up period than those in the control group [18]. Schoultz et al. found a significant decrease in psychological distress and non-significant improvement of QoL and disease activity in patients with IBD allocated to MBCT compared to the waitlist control condition [19]. Two additional RCTs examining MBCT in IBD were conducted after the meta-analysis [20, 21]. Ewais et al. showed that depressed young adults with IBD were less depressed and stressed after MBCT, with an improvement in coping but not in QoL [20]. Finally, in a recent study of Bredero et al., fatigued IBD patients experienced significantly lower levels of fatigue after MBCT compared to the waitlist group [21]. In none of these studies sleep quality was an outcome of interest. Due to the limited evidence, it seems warranted to conduct further research to the effectiveness of mindfulness in patients with IBD, particularly focused on psychological distress and sleep quality.

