### Randomisation and blinding

Randomisation is computerised using CastorEDC [26], an Electronic Data Capture program complying with all regulatory guidance [27]. Participants are allocated using a 1:1 randomisation ratio scheme. Randomisation is stratified for hospital, sex and type of IBD. In order to ensure balanced groups, block randomisation with block sizes of either 2, 4 or 6 are used. Participants cannot be blinded to allocation. For reasons of coordination and logistics, randomisation is performed by a member of the research team, and the research team has therefore access to the information about the assigned group.

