#### Cost-effectiveness

The cost-effectiveness evaluation will be carried out from both a healthcare and societal perspective considering direct as well as indirect costs. Data on resource use (healthcare uptake) and productivity losses will be collected with the TiC-P. Total costs, measured with the TiC-P will be estimated using an incremental bottom-up micro-costing approach, where costs for each patient will be obtained by multiplying information on each element of service with standard costs, based on the Dutch guideline for costing research [67]. We will consider three types of costs: (1) intervention costs of offering MBCT; (2) costs related to healthcare uptake; and (3) costs stemming from productivity losses due to absenteeism. The recall period will be four weeks at baseline, and will consist of three months (the entire period between each follow-up assessment) at 3, 6, 9 and 12 months follow-up. Health related QoL data (based on EQ-5D) from baseline up till 12 months will be used to calculate QALYs using the trapezium rule. Overall mean and median costs and health related QoL will be compared across the conditions and where relevant, differences will be calculated inclusive of 95% confidence intervals. Incremental cost-effectiveness will be determined in terms of incremental costs per QALY gained. The Incremental cost-effectiveness ratio will be determined on the basis of incremental costs and effects of MBCT compared to TAU. Bootstrap simulations with 1.000 replications will be used to get uncertainty intervals in our economic evaluation, taking into account the correlations between costs and QALYs. In addition, a cost-effectiveness acceptability curve will be produced to show the probabilities that given a certain value for the cost-effectiveness threshold, either of the tested strategies is the cost-effective option. In case of missing data, we will use multiple imputation methods to estimate the missing values.

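### The required total of 98 matches only a one-sided 5% test, which the plan never declares; a two-sided test at 98 evaluable patients has about 71% unadjusted power.

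*Protocol article*

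**What the plan says.** The protocol article, under Sample size calculation, takes d = 0.51 from a published meta-analysis and concludes: "With an error probability of 0.05, 0.80 power and a 1:1 allocation ratio, the required total sample size is 98". It then averages dropout rates of 11.5% and 44% to 28% and inflates 98 to 136, or 68 per condition. The Randomisation and blinding section confirms equal allocation.

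The primary analysis section specifies a linear mixed model for post-treatment HADS, adjusted for baseline HADS, centre, sex and IBD type. Neither that section nor the sample size section says whether the test is one- or two-sided, and the sample size section gives no baseline-outcome correlation.

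On the source of the effect size, the sample size section says: "Based on the most recent meta-analysis of MBCT in IBD, we anticipate the effect size". The Background describes the same reference as eight trials of mindfulness-based interventions and comments: "However, the variety in MBIs was rather high, none of the studies had psychological distress as primary outcome".

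**The concern.** An error probability of 0.05 with no qualifier is normally read as two-sided. Read that way, d = 0.51 and 80% power call for clearly more than 98 patients. So either the calculation was one-sided and this was not declared, or the stated power is too high for the test that will be run.

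This is the power statement for the only primary outcome. A reader of a null result would take the chance of having missed d = 0.51 to be 20%. Under an unadjusted two-sided test at 98 patients it would be nearer 29%. If a one-sided 5% test was intended, that is a substantive design choice which readers need to know about. A separate analysis plan could name the test, but it could not make the published sentence correct for a two-sided one.

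**Working it through.** **Inputs.** From the sample size section: d = 0.51 (SD = 1), alpha 0.05, power 0.80, 1:1 allocation, 28% dropout (exact mean (11.5 + 44)/2 = 27.75%). Sidedness is not given, so both versions were computed.

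**Step 1: reproduce 98.** The normal approximation is n per arm = 2(z_alpha + z_power)²/d².

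- One-sided: 2(1.645 + 0.842)²/0.51² = 47.5, so 48 per arm, 96 in total. The t-test (noncentral t) needs 48.23, so 49 per arm, **98 in total**. This matches the plan exactly.
- Two-sided: 2(1.960 + 0.842)²/0.51² = 60.4, so 61 per arm, 122 in total. The t-test needs 61.33, so 62 per arm, **124 in total**. Neither gives 98.

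**Step 2: reproduce 136.** 98/(1 − 0.2775) = 135.6, so 136 (98/0.72 = 136.1). The dropout step is consistent. The same step from 124 gives 124/0.7225 = 171.6, or about 172 randomised.

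**Step 3: power at 49 per arm.** The noncentrality is 0.51 × √(49/2) = 2.524.

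| Test at 5% | Normal approximation | t-test |
|---|---|---|
| One-sided | Φ(2.524 − 1.645) = 0.810 | 0.806 |
| Two-sided | Φ(2.524 − 1.960) = 0.714 | 0.705 |

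The effect detectable with 80% two-sided power at 49 per arm is d = 0.57.

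**Step 4: sensitivity to dropout (two-sided t-test, unadjusted, 136 randomised).**

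| Dropout | Evaluable per arm | Power |
|---|---|---|
| 0% | 68 | 0.84 |
| 11.5% | 60.2 | 0.79 |
| 28% (the plan's value) | 49.0 | 0.70 |
| 44% | 38.1 | 0.59 |

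**Step 5: sensitivity to baseline adjustment (two-sided, 49 per arm).** With T0-T1 correlation r, the effective d is 0.51/√(1 − r²). The values of r are assumptions; the document gives none.

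| r | Effective d | Power |
|---|---|---|
| 0.30 | 0.535 | 0.75 |
| 0.40 | 0.556 | 0.78 |
| 0.45 | 0.571 | 0.80 |
| 0.50 | 0.589 | 0.82 |

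These figures ignore clustering within MBCT groups. The primary analysis section allows for it when the intra-cluster correlation is 0.05 or more, and it would lower power.

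**The case against.** The strongest reply is that the document contains no arithmetic error. It never says two-sided, the outcome is worded as a reduction in distress, and under a one-sided test both 98 and 136 reproduce. That stands in part: the 0.71 is conditional on a two-sided test. But wording the outcome as a reduction does not declare a one-sided test, and the stated number holds only under a condition the reader is not told.

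The second reply is that 0.71 is pessimistic. It requires the full 28% loss and no gain from adjusting for baseline HADS, although the plan does adjust. This also stands in part, as steps 4 and 5 show. However, 28% is the plan's own dropout figure, and the sample size section does not rely on the adjustment.

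Three stronger readings are tempting, and the documents do not support them.

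- A reader might infer that the true type II error is 0.29. That holds only for an unadjusted two-sided test at 98 patients, and the planned model is adjusted.
- A reader might take the 95% intervals as proof that the primary test is two-sided. The phrase "differences will be calculated inclusive of 95% confidence intervals" is from the Cost-effectiveness section and concerns costs and health-related quality of life. It does not govern the HADS test.
- A reader might conclude that 0.51 is not an MBCT effect. The two descriptions of the source do clash, but whether 0.51 is an overall or a subgroup estimate cannot be settled without the cited meta-analysis.

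**Conclusion.** The concern holds as an undeclared one-sided calculation with a conditional loss of power. The required total of 98 is the one-sided 5% t-test answer, and no section declares such a test. Under a conventional two-sided 5% test the requirement is 124 evaluable patients, 26 more than stated. Unadjusted power at 98 is then about 0.71 (0.705 by t-test, 0.714 by normal approximation), roughly 9 points below the stated 0.80.

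The shortfall assumes d = 0.51, the plan's 28% dropout and no gain from baseline adjustment. An assumed T0-T1 correlation of about 0.45 would close it, before any allowance for clustering. The document offers no such value, so the stated 0.80 is unsupported for a two-sided test rather than shown to be unattainable.

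**What to change.** State in the sample size section, and repeat in the results paper, whether the primary HADS test is one- or two-sided, and give the matching power.

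- If two-sided: report about 71% power for d = 0.51 at 98 evaluable patients, unadjusted (80% for d of about 0.57). Alternatively, report the power of the baseline-adjusted analysis with its assumed T0-T1 correlation written down.
- If a one-sided 5% test was intended: declare it explicitly. The figures 98 and 136 can then stand.

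As a separate edit, reconcile the sample size section's description of the source of d = 0.51 with the Background, and say which estimate in the meta-analysis it is.

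The cost is a few sentences. Recruitment was completed in September 2022, and no extra patients are needed. The downside, if the test is two-sided, is a less favourable stated power.

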#### Treatment effects at post-treatment: primary outcome

All analyses will be performed and reported according to the CONSORT guidelines, i.e. primarily on intention-to-treat basis. Treatment effects on the primary outcome (psychological distress at post-treatment, assessed with the HADS) will be analysed using Linear Mixed Effect models, with time, group (MBCT + TAU versus TAU) and Group*Time interaction effects added as fixed effects, while controlling for baseline HADS score and stratification variables (i.e. centre, sex, IBD type). To account for possible dependency caused by clustering in intervention groups, we will add ‘group’ as a random effect if the intra-cluster correlation ≥ 0.05. Restricted maximum likelihood will be used as estimation method to handle missing data. Effect sizes will be calculated using Cohen’s *d*, with values of 0.20–0.50 indicating small effects, 0.50–0.80 moderate effects, and > 0.80 large effects [73]. Cohen’s *d* will be calculated by dividing the adjusted group difference between the means at T1 by the pooled standard deviation at T0.

We will also perform a per-protocol analysis selecting all participants who completed at least half of the MBCT sessions (4 or more) for those assigned to the MBCT condition and inversely, all who have not participated in any mindfulness intervention for those assigned to the TAU condition.

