#### Treatment effects at post-treatment: secondary outcomes

Treatment effects on the secondary outcomes (subjective sleep quality (PSQI, ISI), fatigue (FACIT-F), IBD-related QoL (SIBQ), perceived control over IBD (IBD-control), disease activity (HBI, SCCAI, laboratory results), repetitive negative thinking (PTQ), mindfulness skills (FFMQ-SF), self-compassion (SCS-SF), positive mental health (MHC-SF, FACIT-F QoL domains) and objective sleep parameters: TST, SE, SOL, WASO, relative and absolute duration of REM, and relative and absolute duration of deep sleep at post-treatment will be analysed using separate Linear Mixed Effect models, with time, group (MBCT + TAU versus TAU) and Group*Time interaction effects added as fixed effects, while controlling for baseline score of the variable of interest and stratification variables (i.e. centre, sex, IBD type). The same parameters as in the primary analysis will be used for these analyses. In addition, we will use regression analyses to investigate whether more mindfulness practice (MAQ) is also associated with better outcomes.

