#### Treatment effects at follow-up

In order to investigate consolidation of the treatment effects over time on both the primary outcome (psychological distress) and secondary outcomes (all secondary outcomes except objective sleep parameters) we will again perform linear mixed effect models with time (T1, T2, T3, T4), group (MBCT + TAU versus TAU) and Group*Time interaction, including the same parameters as mentioned above and controlling for baseline levels and stratification variables. Restricted maximum likelihood will be used as estimation method to handle missing data. Cohen’s *d* will be calculated by dividing the adjusted group difference between the means at T4 by the pooled standard deviation at T0.

We also aim to examine the effect of MBCT on recurrence of disease activity (flares). Therefore, we will perform a proportional hazards model (i.e. Cox regression analysis) to analyse the differences between MBCT + TAU and TAU alone in time to flare within the 12-months study period.

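### If the post-treatment model uses T0 and T1 as outcome rows and tests Group-by-Time, the course random intercept cancels from that test and does not protect it against clustering

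*Protocol article*

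**What the plan says.** All of this is in the Protocol article, under Statistical analysis.

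- **Primary outcome, fixed effects.** A linear mixed model "with time, group (MBCT + TAU versus TAU) and Group*Time interaction effects added as fixed effects". T0 HADS and the three stratification factors enter as covariates. The levels of time are not given.
- **Primary outcome, clustering.** "To account for possible dependency caused by clustering in intervention groups, we will add" a term the article calls 'group' "as a random effect if the intra-cluster correlation ≥ 0.05". The same word also names the treatment arm; here it must mean the MBCT course. No course-by-time term is mentioned.
- **Primary outcome, effect size.** Cohen's d is obtained by "dividing the adjusted group difference between the means at T1 by the pooled standard deviation at T0". This is the only contrast named. The section does not say whether the decision rests on it or on Group-by-Time.
- **Secondary outcomes.** The same fixed effects are written out again, objective sleep parameters included, and "The same parameters as in the primary analysis will be used for these analyses".
- **Follow-up.** A separate analysis: "we will again perform linear mixed effect models with time (T1, T2, T3, T4"), controlling for baseline.

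Elsewhere, the section on the MBCT intervention sets courses of eight to ten participants, and Table 1 places the EEG headband at T0 and T1 only.

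**The concern.** A course effect (teacher, group atmosphere, shared sessions) can exist only once the course has run. In this design it is therefore present at T1 and absent at T0, and present only in the MBCT arm. A single random intercept per course models something else: a shift common to all of a course's rows, before and after treatment.

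If both visits are outcome rows, Group-by-Time is a difference in change, and anything common to both visits drops out of it. The term meant to guard against clustering then adds nothing to that contrast's standard error. This is separate from the 0.05 trigger: fitting the term in every case would not repair it. At stake are confidence intervals that are too narrow and too many false-positive claims, for the primary outcome and for every post-treatment secondary outcome that reuses the specification.

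**Working it through.** **Which rows does the model use?**
- T1 alone: neither time nor Group-by-Time can be estimated.
- T1 to T4: this would repeat the model defined separately under Treatment effects at follow-up.
- T0 and T1: consistent with both points. Sleep efficiency and sleep onset latency also get time and Group-by-Time. The Sleep quality and fatigue section derives these two from the headband, not the wristband, and the headband is worn only at T0 and T1. For them, no other pair of visits exists.

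T0 and T1 is therefore the best-supported reading, but it is an inference.

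**The plan's own figure.** No error rate is stated for a clustered analysis. The sample size section gives 98 for d = 0.51, alpha 0.05 and power 0.80. A t-based calculation returns 98 with one-sided 0.05 and 124 with two-sided 0.05; 98/0.72 = 136.1 matches the stated 136. Sidedness is not written, so the two-sided figures below are an assumption.

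**Why the intercept cancels.** For participant i in course k, the fitted model has
- T0: mean + s_i + c_k + error
- T1: mean + s_i + c_k + error

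The change contains no c_k. In reality T1 carries a course effect u_k that T0 lacks, so the change contains u_k and its variance goes unmodelled.

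**Analytic size.** Take unit variance at both visits, rho = course share of T1 variance, r = baseline-to-T1 correlation, m = analysed participants per course, and TAU unclustered. Change has variance 2 − 2r, so
- ICC of change = rho/(2 − 2r)
- variance inflation of the difference in change = 1 + (m − 1) × ICC of change/2
- two-sided error = 2 × [1 − Φ(1.96/√inflation)]

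| rho | r | m | ICC of change | inflation | 1.96/√inflation | error |
|---|---|---|---|---|---|---|
| 0.05 | 0.5 | 6 | 0.050 | 1.125 | 1.848 | 6.5% |
| 0.05 | 0.6 | 8 | 0.0625 | 1.219 | 1.775 | 7.6% |
| 0.10 | 0.6 | 8 | 0.125 | 1.4375 | 1.635 | 10.2% |
| 0.15 | 0.7 | 10 | 0.250 | 2.125 | 1.345 | 17.9% |

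The first and last rows bound the range examined. With one-sided 0.05, the two middle rows become 1 − Φ(1.645/1.104) = 6.8% and 1 − Φ(1.645/1.199) = 8.5%: smaller, same direction.

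**Check on the HADS scale.** Assume SD 5 at T0 and 6 at T1, r = 0.6, 68 per arm and 8 courses. Change variance = 25 + 36 − 2(0.6)(5)(6) = 25, so the SE ignoring courses is √(50/68) = 0.86.
- ICC 0.05: course variance 1.8; true SE = √(23.2/68 + 1.8/8 + 25/68) = 0.97
- ICC 0.10: course variance 3.6; true SE = √(21.4/68 + 3.6/8 + 25/68) = 1.06

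The SE is 11% and 19% too small, implying error of about 8.2% and 11.4%.

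**REML simulation.** 2,000 null trials per row, course effect only at T1 in the MBCT arm, critical value 1.96. Models A to C have T0 and T1 rows and test Group-by-Time. A: participant and course intercepts. B: A plus the baseline covariate. C: A with a course effect acting only at T1. D: T1 as the only outcome row, baseline covariate, course effect on the MBCT arm.

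| rho | r | courses × size | A | B | C | D |
|---|---|---|---|---|---|---|
| 0 | 0.5 | 8 × 6 | 4.5% | 6.2% | 4.0% | 3.8% |
| 0.05 | 0.5 | 8 × 6 | 6.8% | 9.0% | 5.2% | 5.5% |
| 0.10 | 0.5 | 8 × 6 | 8.8% | 11.0% | 6.3% | 6.6% |
| 0.05 | 0.6 | 8 × 8 | 7.8% | 9.6% | 5.8% | 5.6% |
| 0.10 | 0.6 | 8 × 8 | 10.4% | 12.0% | 6.1% | 6.2% |
| 0.10 | 0.7 | 8 × 8 | 11.5% | 13.0% | 6.2% | 6.5% |
| 0.05 | 0.7 | 7 × 10 | 9.8% | 11.4% | 5.8% | 6.6% |
| 0.15 | 0.6 | 8 × 8 | 12.2% | 15.0% | 6.8% | 6.7% |

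Column A isolates the cancellation. Column B is closest to the written model, but its 6.2% at zero clustering shows that using baseline as both row and covariate distorts the test on its own. Model D without a course effect gave 7.3 to 14.2% in the rows with clustering, so the term does real work there.

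**The case against.** The strongest reply is that the article states none of the three premises.

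- **Time levels.** The model controls for baseline, and the one model whose levels are listed keeps T0 out of the rows. If the primary model does the same, the course term enters the arm contrast and works nearly as intended (column D, 5.5 to 6.7% under clustering). This stands as a possibility. It does not explain how Group-by-Time is fitted to headband outcomes, and those sleep models control for baseline too.
- **Tested contrast.** The only named contrast is the T1 difference, from which the intercept does not cancel. In the T0/T1 model without the baseline covariate that contrast had about 6 to 9% error. So a reader who infers that the stated term gives no protection at all goes too far. With the covariate, as written, the T1 contrast was worse (17.0 to 22.2%), but it was already 13.8% at zero clustering. That excess comes largely from the double use of baseline and should not be charged to the course term.
- **Form of the random effect.** An article may leave a course-by-time term to the full protocol or SAP. That is fair, so the point concerns the term as described, not an omission.
- **Inputs.** ICC, correlation and analysed course size are not in the document. Only the eight-to-ten course size is, and with 68 in the arm it makes 7 to 8 courses reasonable.

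**Conclusion.** The point holds conditionally. If T0 and T1 are both outcome rows, as the text best supports, and Group-by-Time is the test, a plain course intercept does not account for course effects in that test. Two-sided error is then roughly 7 to 13% instead of 5% (analytic range 6.5 to 18%), assuming ICC 0.05 to 0.15, correlation 0.5 to 0.7, 7 to 8 courses and a course effect only after T0. Using baseline HADS as both outcome row and covariate is a second, separate source of distortion.

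A reader might infer that the trial's primary test is known to run at a particular inflated error. The document does not support that: time levels, tested contrast, sidedness and the exact random term are unstated, and the percentages depend on assumed inputs. It does support changing the specification before analysis, because the most natural implementation of the text fails and the repair is simple.

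**What to change.** 1. State the time levels of the post-treatment model and name the adjusted group difference at T1 as the primary contrast. This already matches the definition of Cohen's d.
2. Use T1 HADS as the outcome row and T0 HADS only as a covariate. Time and Group-by-Time then leave this model.
3. Put the course random effect on the MBCT arm only, set to zero for TAU, with Satterthwaite or Kenward-Roger degrees of freedom. The 5.5 to 6.7% left in column D under clustering used a normal critical value with only 7 to 8 courses.
4. If T0 rows are kept, drop the baseline covariate and replace the shared intercept with a course effect that acts only after baseline (column C, 5.2 to 6.8% under clustering).
5. Apply the same specification to all secondary post-treatment outcomes.

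The cost is a clarification of the analysis text and a small change to model code, with no new data. The downside is a wider, correct confidence interval when course effects exist.

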### Intervention: MBCT

The MBCT program is based on the protocol published by Segal, Williams and Teasdale [14]. The program consists of eight weekly 2.5 hour sessions, a six hour silent day between session 6 and 7, and daily home practice of 45 minutes guided by audio files. Groups consist of eight to ten participants. Materials are adjusted to include IBD-related examples. The course is offered in the cities where patients are treated (Nijmegen, Arnhem and ‘s-Hertogenbosch) and taught by qualified teachers according to the advanced criteria of the Association of Mindfulness-Based Teachers in the Netherlands and Flanders [28]. These criteria include a minimum of 150 hours of education in MBSR/MBCT (entailing theoretical background, skills practice, supervision and reflection), a minimum of three years of personal meditation practice and attending retreats, and providing a minimum of two courses per two years. All mindfulness teachers participated in a kick-off meeting before the start of the trial, in which the trial-specific MBCT protocol was discussed. Peer supervision meetings are organised twice per MBCT course during the intervention phase of the trial. Teaching sessions are recorded and a random sample of sessions will be rated by two independent raters using the Mindfulness-Based Interventions: Teaching Assessment Criteria (MBI:TAC) [29]. Participation of the training can be discontinued on participant’s request at any time. If so, the participant is encouraged to complete further assessments of the study.

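### The course effect in the MBCT arm enters the primary model only if the ICC reaches 0.05, a test that 7 to 9 courses cannot support; the gain from dropping the cut-off is modest but cheap

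*Protocol article*

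**What the plan says.** Under Intervention: MBCT, "Groups consist of eight to ten participants". TAU patients attend no course during the trial.

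Under Treatment effects at post-treatment: primary outcome, the plan recognises the consequence ("To account for possible dependency caused by clustering in intervention groups") but makes the remedy conditional: the course enters "as a random effect if the intra-cluster correlation" is 0.05 or more. The random effect is called 'group', which is also the name of the treatment-arm fixed effect in the same paragraph.

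The rule extends to the secondary outcomes ("The same parameters as in the primary analysis will be used for these analyses"), and the section on follow-up effects likewise refers back to the earlier specification.

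The Sample size calculation section starts from the effect size ("we anticipate the effect size of the reduction of psychological distress to be Cohen’s *d* = 0.51") and continues "With an error probability of 0.05, 0.80 power and a 1:1 allocation ratio, the required total sample size is 98". It then averages two dropout rates ("These rates were averaged, i.e. 28"%) and arrives at "our corrected sample size is N = 136 (n = 68 per condition"). No ICC, course size or design effect appears there, and no ICC is assumed anywhere else in the article.

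**The concern.** Patients taught together may end up with correlated outcomes, and the plan accepts this. The difficulty is the decision rule. An estimated ICC below 0.05 from seven or eight courses is weak evidence that courses do not differ. When it leads to the course term being dropped, the primary standard error treats patients in the same course as independent.

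A true ICC around the cut-off is not negligible at this course size. With nine per course it raises the variance of the MBCT-arm mean by a factor of 1.4, and the variance of the treatment difference by 1.2. At stake are the width of the primary interval in trials where the term is dropped, the same for the secondary and follow-up models, and a power statement that silently assumes no clustering.

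**Working it through.** **Inputs from the article.** d = 0.51, alpha 0.05 (sidedness not stated), power 0.80, 1:1 allocation, 98 evaluable, 28% dropout, 136 randomised (68 per arm), courses of 8 to 10, cut-off 0.05.

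**Input assumed.** The true ICC, taken as 0.02, 0.05 and 0.10.

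**1. The plan's own figure.** A one-sided two-sample t-test with d = 0.51 and power 0.80 needs 49 per arm, or 98 in total. Then 98/(1 - 0.28) = 136.1, stated as 136. The match needs a design effect of exactly 1, so clustering is not allowed for. (A two-sided test would need 122-124; that is a separate matter.)

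**2. Number of courses.** 68/10 = 6.8 and 68/8 = 8.5, so about 7 to 9. With 49 completers, seven courses hold 7 each.

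**3. Effect of ignoring a real course effect.** Only the MBCT arm is clustered:
- MBCT-arm design effect: DE = 1 + (m - 1) x ICC
- Variance ratio for the treatment difference: VR = (1 + DE)/2
- At m = 9, ICC 0.05: DE = 1.40, VR = 1.20, so the true SE is √1.20 = 1.095 times the unclustered one.
- For m = 8 to 10, the true SE is 1.03-1.04, 1.08-1.11 and 1.16-1.20 times the unclustered one at ICC 0.02, 0.05 and 0.10. A nominal 95% interval then covers about 94%, 92-93% and 90-91%.

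**4. How the cut-off behaves.** Null simulation with the MBCT arm nested in equal-sized courses and TAU unclustered, no covariates, and the ICC from one-way ANOVA. Settings: 7 courses of 7 with 49 TAU, and 8 courses of 8 with 68 TAU. At a true ICC of 0.05 the estimate has a standard deviation of about 0.09-0.10, roughly twice the cut-off.

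| True ICC | Term dropped | Two-sided error when dropped | Error when kept (Satterthwaite) |
|---|---|---|---|
| 0.02 | 67-70% | 5.7-5.9% | below 2% |
| 0.05 | about 56% | about 7% | about 2% |
| 0.10 | 37-40% | 9-10% | 2.5-2.7% |

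Over both branches at ICC 0.05-0.10, error is 4.8-5.3% with Satterthwaite degrees of freedom in the kept branch and 5.2-6.1% with residual degrees of freedom. The article does not say which would be used.

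**5. Always fitting the course effect, same simulation.** With the course variance held at zero or above, overall error is 4.4-4.8% at ICC 0.05-0.10. In the trials where the estimate falls below 0.05, error is still 6.2-6.3% at ICC 0.05 and about 8% at 0.10. The two rules reach different significance decisions in about 0.5% of trials.

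**6. Power at 49 per arm, one-sided as in step 1.** Noncentrality without clustering is 0.51 x √(49/2) = 2.524; with clustering, divide by √VR. For ICC 0.05 and m = 7, VR = 1.15: 2.524/1.072 - 1.645 = 0.709, so power is 0.76. For m = 9, VR = 1.20: 2.524/1.095 - 1.645 = 0.660, so power is 0.745 (0.74 from the t distribution). Over m = 7 to 9:
- ICC 0.02: about 0.78
- ICC 0.05: 0.74-0.76
- ICC 0.10: 0.68-0.71

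**The case against.** The strongest reply is that type I error belongs to the whole procedure, and over both branches it is near 5%. The 7-10% figures arise only after sorting trials by their variance estimate, which makes almost any estimated-variance method look bad. Much of the excess survives the remedy: with so few courses, an always-fitted model estimates zero course variance in a third or more of trials at ICC 0.05 and then returns the unclustered interval. All of this stands. It limits the point to a modest gain. It does not make the cut-off a good rule, because near-5% overall error relies on Satterthwaite degrees of freedom that the article does not name, and the cut-off adds a data-dependent choice to the primary model for no benefit.

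A reader might infer three stronger things that the document does not support.
- **That the primary test is invalid overall, or that removing the cut-off restores exact coverage.** Steps 4 and 5 show neither.
- **That clustering takes power down to 0.63-0.64.** That is a two-sided figure at ICC 0.05. Two-sided power at 98 is already about 0.71 with no clustering, so clustering accounts for only 0.06-0.08. The sidedness gap is a separate issue and is not counted here.
- **That 0.80 power is lost once any course effect exists.** The primary model adjusts for baseline HADS. With an assumed baseline-to-follow-up correlation of 0.5, one-sided power at ICC 0.05 would be 0.82-0.84; at 0.3 it would be 0.77-0.79. The sample size section claims no such gain, but the analysis may deliver one.

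It is also fair that the double use of 'group' can be resolved from context, and that an article may leave degrees of freedom and the coding of TAU patients to the analysis plan. The cut-off itself, however, is stated.

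**Conclusion.** The point holds in a limited form. The article fixes a cut-off that 7 to 9 courses cannot apply reliably. At an assumed true ICC of 0.05, whether the course term stays in the primary model is close to a coin toss, and when it is dropped the two-sided error is about 7% (9-10% at ICC 0.10). Overall error stays near 5%, or up to about 6% with residual degrees of freedom, and part of the conditional error comes from having few courses rather than from the cut-off. If the true ICC is 0.02 or less, the effect is small, with coverage about 94%.

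Separately, the stated 0.80 power assumes no clustering, although the analysis section anticipates it. All sizes rest on assumed ICCs, equal course sizes and a simulation without covariates. This is a worthwhile, inexpensive improvement to the primary model, not a threat to the trial's validity.

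**What to change.** - Delete the 0.05 condition. Always fit a random effect for MBCT course in the MBCT arm only (partially nested; TAU patients have none), with Satterthwaite or Kenward-Roger degrees of freedom. Apply this to the primary, secondary and follow-up models.
- Call it MBCT course, so that it cannot be confused with the treatment arm, and report the estimated ICC.
- State that the 0.80 power assumes no clustering, and give it over a range of ICCs as in step 6. Recruitment ended in September 2022, so this helps interpretation and cannot change the sample.

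The cost is a few lines of model specification, and slightly wider intervals than necessary if the true ICC is near zero.
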